### Power analyses

The expected sample (475 paired counties, up to 4 respondents per county, resulting sample size of ~ 3800) and the response rate of 50% gives an expected sample of 1900 respondents. Given that anywhere from 0 to 4 respondents may complete the survey in any given county, with a 50% overall response rate, we anticipate that 712 counties will have at least one respondent who completes the survey. We used a conservative (higher than expected) intraclass correlation coefficient of 0.1 for addressing clustering of agencies within counties.

For county-level analysis, an effect size of 0.2, power of 0.8, confidence level of 95%, and statistical significance level of 0.05 were used to calculate the minimum sample size. Repeated measures analysis required a minimum total sample size of 304 counties. For logistic regression and other nonlinear predictive models, depending on the type and quantity of variables used in the model, the minimum total sample size required varied between 156 and 489 counties. With attrition, our calculations showed a power of 0.9 and more for most county-level analyses.

For agency-level analysis, a conservative agency-level effect size estimate (*d* = 0.1), a power of 0.8, confidence level of 95%, and significance level of 0.05 were used to calculate the minimum required sample size. Repeated measures analysis comparing respondents from Stepping Up and comparison counties resulted in a minimum sample size of 524 respondents. When comparing the response measures, measured at the agency level, over time, a minimum sample size of 1200 respondents is required. For predictive logistic regression and other nonlinear predictive models, the minimum sample size varied between 673 and 1100 respondents. Given the larger sample size of this study, our calculations showed a power higher than 0.9 for agency-level analyses.

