### Analysis plan

#### General approaches

Primary tests will be 2-sided with α = 0.05. Analysis approaches accommodate nested and repeated measures data. We will examine predictive associations between Stepping Up membership, hypothesized target mechanisms, and implementation outcomes over time. We will use general linear models and generalized linear mixed models (GLMM) when the dependent variables are continuous and noncontinuous, respectively. GEE will be used instead when distributional assumptions are not met. For non-aggregated dependent variables reported at the agency level (i.e., hierarchical data), a random intercept growth hierarchical linear model (GHLM) will be fitted. All analyses will covary: (1) Wave 1 (baseline) values of dependent variables, (2) months since the county joined Stepping Up, (3) the matching score, (4) an indicator representing whether a the county shares their mental health administrator with other counties, and (5) a similar indicator for shared justice roles across counties.

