##### Secondary

We will test the hypothesis that Stepping Up counties will show faster rate of improvement in the *use/functioning of interagency teams* (i.e., total scores on the integrated NCJTP Relationship Assessment Inventory-IOR measure) than control counties using the same statistical techniques. We will test the hypothesis that Stepping Up counties will show faster rate of improvement in *common goals and mission across agencies* (i.e., agreement between perceived agency and county priorities) than comparison counties using GLMM or GEE. We will conduct similar analyses of agreement among respondents within each county on the importance of mental health treatment for justice-involved individuals. We will test the hypothesis that Stepping Up counties will show faster rate of improvement in *system integration* (score of 6 or more on the Relationship Assessment Inventory score) using GEE. Separate secondary analysis will compare rates of change in the use of the same screening and assessment instruments by multiple agencies in Stepping Up and comparison counties.

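### The agency-level logistic minimums (673 to 1100) and the unqualified power above 0.9 do not follow from d = 0.1 for a Stepping Up versus comparison contrast on a binary outcome

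*Protocol article*

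**What the plan says.** All power figures are in the Protocol article, Methods, Power analyses.

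- **Agency level:** the inputs are "a conservative agency-level effect size estimate (*d* = 0.1), a power of 0.8" and a significance level of 0.05. The logistic result is "For predictive logistic regression and other nonlinear predictive models, the minimum sample size varied between 673 and 1100 respondents". The section closes with "Given the larger sample size of this study, our calculations showed a power higher than 0.9 for agency-level analyses".
- **County level:** the inputs begin "For county-level analysis, an effect size of 0.2, power of 0.8, confidence level of 95" percent. The metric of the 0.2 is not named. For logistic and other nonlinear models, "the minimum total sample size required varied between 156 and 489 counties", and this is said to vary "depending on the type and quantity of variables used in the model". Power of 0.9 or more is claimed for most county-level analyses, not all.
- **Expected sample:** 1900 respondents and 712 counties with at least one respondent, with an intraclass correlation of 0.1 for agencies within counties.

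The binary endpoint is system integration, a dichotomised Relationship Assessment Inventory score that the Measures section classes as agencies nested within counties. Under Aim 1a, Secondary, its rate of improvement is compared between Stepping Up and comparison counties ("score of 6 or more on the Relationship Assessment Inventory score) using GEE"). General approaches adds "Primary tests will be 2-sided with α = 0.05" and adjusts every analysis for the Wave 1 value.

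**The concern.** The predictor of interest for system integration is a 1:1 group indicator. A difference of 0.1 standard deviations between two equal groups is a small effect, and a binary outcome usually needs several thousand respondents to show it. The article gives a minimum of roughly 700 to 1100 and then power above 0.9 for every agency-level analysis, so a reader takes the binary comparison to be comfortably powered.

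If it is not, a null result on system integration would be given more weight as evidence of no effect than the data can bear. That applies to the mechanism comparison and to the secondary mediation analysis that uses the same measure.

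**Working it through.** **Inputs from the article.** Two-sided α = 0.05; power 0.80; d = 0.1 (agency); effect 0.2 (county); 1:1 allocation; 1900 respondents; 712 counties; intraclass correlation 0.1.

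**Assumptions, not in the article.** Event rate 0.5 unless stated (the most favourable case for the odds-ratio conversion); within-unit correlation ρ between waves of 0.5 to 0.8; all 1900 respondents present at every wave; the county effect of 0.2 read as h.

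**Constant.** (1.960 + 0.842)² = 7.849.

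**1. Attempt to reproduce the printed minimums.**
- Logistic model, continuous predictor per SD: N = 7.849 / [p(1−p)β²], with β = d·π/√3. At d = 0.1, β = 0.1814 (odds ratio 1.20), so N = 7.849 / (0.25 × 0.0329) = 954. At 0.2, β = 0.3628 (odds ratio 1.44) and N = 239. As p = 0.5 gives the smallest N, neither 673 nor 156 can come from this model.
- Group indicator with the effect doubled: its variance is 0.25, which multiplies N by 4, and doubling the effect divides N by 4. The result is again 954 and 239.
- Risk differences: 0.26 versus 0.36 gives a total of 670, and 0.18 versus 0.38 gives 156. But the agency effect is labelled d, and no event rates are given.

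No single set of stated inputs returns all four printed figures.

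**2. Single-wave group contrast at d = 0.1.**
- Arcsine scale: N = 4 × 7.849 / 0.1² ≈ 3,140.
- Odds-ratio scale, p = 0.5: N = 4 × 954 ≈ 3,820. By a two-proportion calculation it is 4,394 at a comparison rate of 0.3 and 5,662 at 0.2.
- Power = Φ(h√(N/4) − 1.96) at h = 0.1: 25% at 673, 38% at 1100, 59% at 1900.

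**3. Clustering.** 1900/712 = 2.67 respondents per county. Design effect = 1 + 1.67 × 0.1 = 1.167. Effective N = 1900/1.167 = 1,628. Power = Φ(0.1 × √407 − 1.96) = Φ(2.017 − 1.96) ≈ 52%. On the odds-ratio scale it is about 45%.

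**4. Wave 1 adjustment.** Variance is multiplied by 1 − ρ², so power = Φ(2.017/√(1−ρ²) − 1.96).

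| ρ | h scale | Odds-ratio scale (p = 0.5) |
|---|---|---|
| 0.5 | 64% | 56% |
| 0.7 | 81% | 73% |
| 0.8 | 92% | 86% |

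Power of 0.9 needs 2.017/√(1−ρ²) = 1.960 + 1.282 = 3.242. Then 1−ρ² = 0.387 and ρ ≈ 0.78 on the h scale. It is slightly above 0.8 on the odds-ratio scale.

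Adding Wave 2 changes little for a slope. With exchangeable correlation and an effect growing linearly from zero to its full size at Wave 3, the variance factor is (1−ρ)/[1.25 − 2.25ρ/(1+2ρ)]. That is 0.73, 0.51 and 0.36 at the three correlations, against 0.75, 0.51 and 0.36 above.

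**5. County level, h = 0.2, 712 counties.** Single-wave power = Φ(0.2 × √178 − 1.96) = Φ(0.708) ≈ 76%. Adjusted for Wave 1 at ρ = 0.7, it is about 92% even on the odds-ratio scale.

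**6. Detectable effect at 80% power, single wave.** h = 2 × 2.802/√N: 0.14 at 1,628 effective respondents and 0.21 at 712 counties.

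**The case against.** The strongest reply is that the article never ties the logistic ranges to system integration. It attaches them to predictive models whose size depends on the variables used, and such models may include continuous scores (0 to 12, 0 to 28, 0 to 54) as predictors. The minimum it names for Stepping Up versus comparison respondents is the separate figure of 524. This stands for the ranges themselves: if they serve other models, they need only a label. It does not rescue the closing agency-level power statement, which has no exception and so covers the binary group contrast.

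The planned test is also a longitudinal slope contrast adjusted for Wave 1, not a single-wave comparison. This stands too. On the h scale the adjusted test reaches 80% at a correlation of about 0.7. A reader might infer that the test is close to a coin flip, or that 3,140 respondents and 785 counties (4 × 7.849/0.2²) are its true minimums. The documents support neither, because both describe a single unadjusted wave.

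A reader might also infer that the authors used a continuous-predictor formula by mistake. That cannot be shown. A continuous predictor at d = 0.1 and a group contrast at d = 0.2 are algebraically the same calculation, and neither gives 673 or 156. Nor can it be shown that this is an error separate from any behind the repeated-measures minimums.

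A condensed article may leave event rates and correlations to the fuller plan. The point here is not their absence, but that the printed effect, minimum and power do not agree without a demanding value for one of them.

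**Conclusion.** The concern holds in a limited form. At d = 0.1, 673 to 1100 respondents do not give 80% power for a single-wave group contrast on a binary outcome: on the h scale they give 25% to 38%. The unqualified power above 0.9 with 1900 respondents requires a within-unit correlation of about 0.8 or higher. At 0.5 to 0.7, adjusted power is about 64% to 81% on the h scale and 56% to 73% on the odds-ratio scale. These values assume full response at each wave, and the odds-ratio values assume 50% prevalence; at prevalences further from 50% they are lower.

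The county-level part is secondary. Single-wave power of about 76% does not contradict a claim made only for most analyses, and 0.9 can be met at a correlation of about 0.7.

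System integration is a secondary mechanism and secondary mediator, so the primary tests are not affected by this point. The cause of the discrepancy is not established.

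**What to change.** 1. Recompute the logistic minimum and power for the planned test: the baseline-adjusted slope contrast between groups on the binary endpoint, with intraclass correlation 0.1, over a stated range of prevalence and within-unit correlation.
2. Replace the blanket agency-level power statement with that result. Alternatively, report the effect detectable at 80% power; for a single wave this is h of about 0.14 with 1900 respondents and intraclass correlation 0.1, and about 0.21 with 712 counties.
3. If 673 to 1100 and 156 to 489 belong only to other predictive models, say so beside the figures.
4. Do not substitute 3,140 or 785 as minimums for the longitudinal test.

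The cost is one recalculation and a reworded paragraph. No counties or respondents need to be added. The price is a less favourable stated power for the binary endpoint.

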### Analysis plan

#### General approaches

Primary tests will be 2-sided with α = 0.05. Analysis approaches accommodate nested and repeated measures data. We will examine predictive associations between Stepping Up membership, hypothesized target mechanisms, and implementation outcomes over time. We will use general linear models and generalized linear mixed models (GLMM) when the dependent variables are continuous and noncontinuous, respectively. GEE will be used instead when distributional assumptions are not met. For non-aggregated dependent variables reported at the agency level (i.e., hierarchical data), a random intercept growth hierarchical linear model (GHLM) will be fitted. All analyses will covary: (1) Wave 1 (baseline) values of dependent variables, (2) months since the county joined Stepping Up, (3) the matching score, (4) an indicator representing whether a the county shares their mental health administrator with other counties, and (5) a similar indicator for shared justice roles across counties.

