#### Aim 1a: comparison of target mechanisms between Stepping Up and non-Stepping Up counties

##### Primary

We will test the hypothesis that Stepping Up counties will show faster rate of improvement in *the use of/ capacity for performance monitoring* (i.e., total scores on our Performance Monitoring measure) than comparison counties, using GLMM or GEE. Analyses will test for differences in slopes (rates of change). Separate secondary analysis will compare rates of change in the adapted Routine Decision-Making scale total score between Stepping Up and comparison counties.

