#### Aim 1b: tests of mediation

##### Primary

We will test the hypothesis that *changes in use of performance measures* (i.e., scores on UPMDC and the adapted Routine Decision-Making scale) will mediate any differences found in *rates of change in primary measures of justice-involved clients receiving behavioral health services, number of EBPPs, and resources available*. These primary mediator analyses will use structural equation models, and path analyses.

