#### Aim 2: comparison of implementation outcomes between Stepping Up and non-Stepping Up counties

##### Primary

We will test the hypothesis that Stepping Up counties will show faster rate of improvement in the number of justice-involved clients receiving behavioral health services than will comparison counties, using GLMM and GEE. Analyses will test for differences in slopes (rates of change) between the two sets of counties.

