##### Secondary

We will separately test the hypotheses that Stepping Up counties will show faster rate of improvement in the *number of behavioral health EBPPs available to* and *resources for behavioral health EBPP for justice-involved individuals* using GLMM, GEE, and GHLM.

We will examine moderators of the effects of Stepping Up participation on our primary outcome (justice-involved clients receiving behavioral health services) using structural equation models. A priori moderators include months between a county joining Stepping Up and study baseline, levels of implementation outcomes at study baseline, type of agency, organizational culture support for innovations (i.e., score on NCJTP Assess Your Organizational Culture scale [38]), jails with their own behavioral health staff, yes/no presence of legislative reforms, counties in states that have mental health diversion funding, and counties with divisions that provide cross-system trainings.

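### The growth model for agency-level outcomes has a random intercept only, although it is to test a difference in slopes between groups of counties, so its standard error can be too small

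*Protocol article*

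**What the plan says.** Under Analysis plan, General approaches, the protocol states for non-aggregated, agency-reported dependent variables that "a random intercept growth hierarchical linear model (GHLM) will be fitted". It mentions no random slope and does not say whether the intercept is for county, agency or both. The same section sets the test level: "Primary tests will be 2-sided with α = 0.05".

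The hypotheses under Aim 1a and Aim 2 concern faster improvement. For the Aim 2 primary outcome: "Analyses will test for differences in slopes (rates of change) between the two sets of counties". The Aim 1a primary paragraph says the same.

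The methods named for each hypothesis differ:
- Aim 1a primary (performance monitoring): "than comparison counties, using GLMM or GEE".
- Aim 2 primary (clients receiving services): GLMM and GEE.
- Aim 2 secondary (number of EBPPs, resources): "using GLMM, GEE, and GHLM".

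The random-intercept growth model (GHLM) is thus tied by name only to the Aim 2 secondary outcomes. Of these, the Measures section treats resources as agency level and the number of EBPPs as a single county value. The same section labels the primary mechanism measures and the services count as agencies nested within counties, so the general rule could bring the GHLM to them too.

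GEE replaces the other models when distributional assumptions fail (General approaches) and is used, possibly weighted, for missing waves (Missing data). Its clustering unit is not given.

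**The concern.** Stepping Up is an exposure of the county. A fair test of whether one group of counties changes faster must set the difference in mean slope against how much slopes vary from county to county. A random intercept absorbs differences in level but not in rate of change. If counties change at different rates, that variation goes partly into the residual, where it is treated as independent from one observation to the next. The slopes shared by agencies in the same county are then not recognised as shared.

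Varying slopes are plausible here. Counties select themselves into a locally adaptable programme, and they had been in it for 1 to 5 years at study baseline (Methods). The plan also lists several candidate moderators of the programme's effect (Aim 2, Secondary). At stake is the nominal 5% level, and the width of the confidence intervals, for any outcome analysed with this model.

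**Working it through.** **Inputs from the protocol.** Three waves (Methods). Two-sided α = 0.05 (General approaches). 1900 expected respondents over 950 counties, so 1900/950 = 2 per county; over the 712 counties expected to respond, 1900/712 ≈ 2.67 (Power analyses). ICC for level 0.1 (Power analyses).

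**Assumed inputs.** The protocol gives no slope variance. Set the residual variance to 1. Let *c* be the county slope variance and *a* the agency slope variance, per wave interval. Let *m* be the number of responding agencies per county. The outcome is continuous and the data balanced.

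**Case 1: three waves as outcomes, agency and county intercepts.** Code time as −1, 0, 1, so that Σt² = 2. Over N counties the true variance of a group's mean slope is [(1/2 + a)/m + c]/N. The model's residual variance becomes 1 + a + c, so it reports (1 + a + c)/(2mN). Hence

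ratio true/model = (1 + 2a + 2mc)/(1 + a + c), and actual size = 2[1 − Φ(1.96/√ratio)].

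The nominal level is reproduced when slopes do not vary: a = c = 0 gives ratio 1 and size 5.0%.

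With a = 0 and m = 2:
- c = 0.05: 1.20/1.05 = 1.143, size 6.7%
- c = 0.10: 1.40/1.10 = 1.273, size 8.2%
- c = 0.25: 2.00/1.25 = 1.600, size 12.1%

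At m = 2.67 the three sizes are 7.4%, 9.7% and 15.2%. At m = 4, c = 0.10 and 0.25 give 12.5% and 20.6%. Agency slope variance alone has less effect: a = 0.10 gives 1.20/1.10 = 1.091, size 6.1%.

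**Case 2: Wave 1 as covariate only, Waves 2 and 3 as outcomes.** The ratio is (2 + a + mc)/(2 + a + c). At c = 0.10 and a = 0:
- m = 2: 2.2/2.1 = 1.048, size 5.6%
- m = 4: 2.4/2.1 = 1.143, size 6.7%

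Agency slope variance alone gives ratio 1, so no inflation.

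**Case 3: three waves, county intercept only.** Agency differences in level now stay in the residual. Assume an agency intercept variance of 0.8 and a county intercept variance of 0.2; the county ICC is then 0.2/(0.2 + 0.8 + 1) = 0.1, the protocol's figure. The within-county mean square is [3(m − 1)(0.8) + (3m − 1) + 2mc]/(3m − 1), and the ratio is (1 + 2mc) divided by it. With m = 2:
- c = 0: mean square 7.4/5 = 1.48, ratio 0.676, size 1.7%
- c = 0.10: 7.8/5 = 1.56, ratio 1.40/1.56 = 0.897, size 3.9%
- c = 0.25: 8.4/5 = 1.68, ratio 2.00/1.68 = 1.190, size 7.2%

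The test is thus conservative at small slope variances and turns anti-conservative at larger ones.

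**Simulation checks.** For case 1 with 712 counties, two agencies and 4000 runs, the random-intercept test rejected in 4.8% (c = 0), 6.7% (c = 0.05) and 8.1% (c = 0.10). A county-level analysis of slopes stayed at 4.7% to 5.4% in all settings run. With unequal numbers of respondents (300 counties, binomial with 4 agencies and probability 0.5, 400 runs per setting), random intercept against GEE with robust errors clustered on county gave 4.8% v 5.0% (c = 0), 5.8% v 4.3% (c = 0.05) and 8.5% v 4.5% (c = 0.10). For case 3 (712 counties, two agencies, 3000 runs) the sizes at c = 0, 0.10 and 0.25 were 2.1%, 3.3% and 7.2%.

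**The case against.** The strongest reply is that this model is not the one named for the primary tests. Those name GLMM and GEE, and the services measure, being a count, would go to GLMM under the protocol's own rule. GEE with robust errors clustered on county holds about 5%, and with a 50% response rate missing waves may bring GEE in often. The candidate moderators are hypotheses to be tested and do not establish that residual slopes vary. All analyses also adjust for the Wave 1 value, which points towards case 2, where the inflation is small.

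Most of this stands, and it limits the point. It does not remove it. The protocol states this random-effects structure outright, so the structure has not been left to a later document. The same general rule can reach the nested primary measures. GEE is conditional, and if it clustered on respondent it would still miss slopes shared within a county.

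A reader might infer that every hypothesis in the plan is a slope contrast exposed to this fault. The protocol does not support that. For the Aim 1b mediation, "These primary mediator analyses will use structural equation models, and path analyses", and the quantitative part of Aim 3 relates implementation strategies to outcomes.

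**Conclusion.** The point holds conditionally and is of moderate severity. Wherever the stated model is used, it makes no allowance for slopes that differ between counties, and its model-based group-by-time standard error can be too small. This use is explicit for the Aim 2 secondary outcomes and possible for the nested primary measures.

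With three waves as outcomes, both intercepts and two agencies per county, type I error is about 7% to 12% for assumed county slope variances of 0.05 to 0.25 of the residual variance. The other readings in the working give smaller, nil or reversed effects.

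A reader might conclude that false positives certainly exceed 5%, or that the primary results are compromised. Neither follows. The protocol gives no slope variance, leaves open the level of the intercept and whether Wave 1 is also an outcome, and names other methods for the primary tests. What can be said is that the stated model protects the 5% level only under conditions that the protocol neither states nor makes likely.

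**What to change.** In General approaches, replace the random-intercept growth model with one that has intercepts for county and agency and a county-level random slope for time. Alternatively, keep the intercepts and base every group-by-time test on robust standard errors clustered on county. State that GEE, including weighted GEE, clusters on county. Say in the same place whether Wave 1 is an outcome as well as a covariate, and whether the GHLM applies to the nested primary measures.

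This is a short change of specification and needs no new data. Its price is somewhat wider confidence intervals, and so some loss of power, if slopes do vary. If they do not, little is lost: in the checks above, the county-clustered analyses kept about 5% either way.
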